### Recruitment

Patients referred by primary care physicians to one orthopedic department (Hässleholm and Kristianstad Hospitals) are examined by trial investigators (orthopedic surgeons) at the outpatient clinic and screened for eligibility. Those with a clinical diagnosis of CTS who have failed treatment with wrist splint and whose symptom severity is judged to warrant surgery are offered to be put on the waiting list for carpal tunnel release. Patients who are willing to undergo surgery are put on the waiting list, which means a waiting time of approximately 3 months. The trial investigator explains the aims, advantages and disadvantages of the trial to eligible patients at the orthopedic department's outpatient clinic. Patients who give informed consent will be allocated to one of the three trial groups. Recruited patients are assigned to a treatment group at the outpatient clinic according to a computer-generated randomization list. Immediately following the allocation the patients will receive the assigned treatment. In patients with bilateral symptoms the most symptomatic hand (as reported by the patient) will be included and in case both hands are equally symptomatic the dominant hand will be included. Patients will not be allowed to enter the trial more than once.

Recruitment to the trial according to the plan described above is believed to ensure the inclusion of a representative sample from the patient population residing in the catchment area. All patients are asked for informed consent before any study procedure is performed. The patients will be recorded in a screening/inclusion/randomization list.

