### Randomization

A computer-generated randomization list of 120 items in blocks of variable sizes (unknown to the investigators involved in recruiting patients) is prepared by the statistician. Based on the list sequentially numbered sealed opaque envelopes containing cards with group assignments are prepared. These sealed envelopes marked with the patients' sequential numbers are kept at the orthopedic department's outpatient clinic. When a patient is enrolled and written informed consent obtained, the nurse opens the envelope with the lowest number and prepares the injection according to the card and then sign date, name and sequential number on the medication list. The nurse preparing the drug is responsible for putting the card in a new envelope marked with the sequential number. This card will be kept in a box with the study medication. As backup, a sealed envelope with the randomization database is kept, together with the study drugs, in the locked area reserved for drugs at the outpatient department. In case the blinding needs to be broken for a patient, the nurse will open the envelope and extract the information for that patient. The envelope will be signed with name and date and given to a monitor.

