### Sample Size

Based on previous studies of surgical outcome in patients with idiopathic CTS the mean improvement in the CTS symptom severity scale at 12 weeks after surgery is about 1.6 (on the 1 to 5 point scale). A mean improvement of less than 0.8 in the CTS symptom severity score cannot warrant recommending steroid injection as an effective alternative treatment. With 90% statistical power, 5% significance level, and two-sided statistical tests, and assuming a standard deviation of 1.0 for the CTS symptom severity score the study can detect a true difference of at least 0.8 point on the CTS symptom severity score between an intervention group and the placebo group when 102 patients have been randomized. The aim will be to enroll 120 patients in the study to account for potential incomplete follow-ups.

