### Statistical Analysis

All patients who have been randomized and have received an injection will be included in the statistical evaluation. Statistical tests will be performed and reported according to the intention-to-treat principle. Data will be presented as mean and standard deviation or median and range, as appropriate, for continuous variables and as numbers and proportions for categorical variables. The primary analysis of the CTS symptom severity score at 10 weeks will be performed using a mixed model analysis of repeated measures (baseline, 5 weeks, 10 weeks) with treatment effect (placebo or Methylprednisolone) and time as fixed factors in a first step and with the interaction term of treatment and time in second step. The results will be presented as differences in mean score change over time (baseline to 10 weeks) and 95% confidence intervals. The secondary analysis of the symptom severity score will be done using a mixed model with treatment (placebo or Methylprednisolone) as a random factor and time (baseline, 5 weeks, 10 weeks, 24 weeks, 52 weeks) as fixed factor and surgery as covariate; first step without interaction terms and second step with two-way interaction of treatment and time. The results will be presented as differences in mean score change over time and 95% confidence intervals.

The primary analysis of rate of surgery will be done using Fisher's exact test (univariate) and logistic regression (multivariate) with adjustment for baseline variables. The issue of multiplicity is addressed by performing the analysis in the following priority; 52 weeks, 24 weeks, and 12 weeks. The results will be presented as differences in the rate of surgery between the groups (Methylprednisolone compared with placebo) and as adjusted odds ratio (and 95% confidence interval) of having surgery at each time point. The possible dose-response relationship with higher effect of high dose will be explored by prioritizing group comparisons. We will conduct the following predefined subgroup analyses; symptom duration (12 months or shorter versus more than 12 months), symptom severity (baseline symptom severity score below 3.0 versus 3.0 or higher), and median nerve conduction abnormality (moderate or severe versus mild or normal).

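### Fisher's exact test for the primary surgery-rate comparisons is valid but conservative at about 40 per arm; Boschloo's exact test would usually recover a few points of power at no cost in type I error

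*Protocol article*

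**What the plan says.** The Primary endpoint section makes the rate of surgery one of two primary endpoints. It is compared pairwise among the three groups, with 52 weeks ranked first, then 24 and 12 weeks. On the method, the Statistical Analysis section says "The primary analysis of rate of surgery will be done using Fisher's exact test (univariate"), and the same sentence adds baseline-adjusted logistic regression. It does not say which of the two decides. Results are to be shown as rate differences and as adjusted odds ratios, with a 95% confidence interval attached to the odds ratio.

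The Sample Size section rests on the symptom score alone. It reaches its target "when 102 patients have been randomized" and then states: "The aim will be to enroll 120 patients in the study to account for potential incomplete follow-ups". No surgery rate, target difference or power is given for the surgery endpoint in any section.

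**The concern.** Fisher's test conditions on both margins of the 2x2 table, although the design fixes only the arm sizes. With arms this small, few p-values are attainable, so the test usually stops short of 5%. What is at stake is efficiency: the surgery rate is a primary endpoint, the sample was not sized for it, and some of the available power goes unused.

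High surgery rates, where Fisher's size is lowest, are conceivable. The Recruitment section says: "Patients who are willing to undergo surgery are put on the waiting list". An unconditional exact test avoids part of the loss and gives the same guarantee on type I error.

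**Working it through.** **Inputs from the protocol**
- Level: "With 90% statistical power, 5% significance level, and two-sided statistical tests" (Sample Size). This is stated for the symptom score; two-sided 5% is assumed to carry over to the surgery-rate tests.
- Arm size: 120 in three groups. The allocation ratio is not stated; if equal, 120/3 = 40 per arm.
- Balance: "A computer-generated randomization list of 120 items in blocks of variable sizes" (Randomization), with analysis of everyone randomized who was injected. Exactly 40:40:40 is therefore not assured, and unequal arms were run too.
- Surgery rates: none given. Values from 30% to 95% are assumptions.

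**The plan's own figure.** For a difference of 0.8 and SD 1.0, n per arm = 2 × (1.960 + 1.282)² × (1.0/0.8)² = 32.8, so 33. With the t distribution, power is 89.3% at 33 and 90.2% at 34 per arm, and 3 × 34 = 102. The stated figure reproduces, but it says nothing about surgery rates.

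**Method: full enumeration of the 2x2 tables**
- With x and y operations in arms of n1 and n2, and s = x + y, each table has conditional probability C(n1,x)·C(n2,y)/C(n1+n2,s). The two-sided Fisher p is the sum over tables with the same s that are no more likely than the one observed. Fisher's test rejects at p ≤ 0.05.
- Size at a common rate π is the sum over rejected tables of Bin(x; n1, π)·Bin(y; n2, π), taken at 1,999 values of π.
- Boschloo's test rejects when the Fisher p is at most c, where c is the largest cut-off whose maximum size is at most 5%. Fisher's own maximum size is below 5%, so c is at least 0.05 and every Fisher rejection is kept. At 40 v 40, c = 0.0707.
- Power is the sum over rejected tables of Bin(x; n1, p1)·Bin(y; n2, p2).

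**Type I error**

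| Arms | Fisher maximum | Fisher below 2% from a common rate of | Boschloo maximum |
|---|---|---|---|
| 40 v 40 | 3.30% | 88.6% | 4.77% |
| 39 v 40 | 4.22% | 92.0% | 4.70% |
| 41 v 39 | 4.22% | 92.0% | 4.89% |
| 37 v 40 | 3.96% | 94.3% | 4.98% |
| 36 v 42 | 4.07% | 94.4% | 4.93% |

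At 40 v 40, Fisher's size is 2.82% at a common rate of 80%, 2.55% at 85% and 1.68% at 90%. Boschloo's size at 90% is 3.07%.

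**Power.** Rates are assumed. With unequal arms, the first-named arm has the higher rate. Gains are in percentage points and come from unrounded values.

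| Rates | 40 v 40, Fisher to Boschloo | Gain 40 v 40 | Gain 39 v 40 | Gain 41 v 39 | Gain 37 v 40 |
|---|---|---|---|---|---|
| 90% v 70% | 53.4% to 59.2% | 5.8 | 2.3 | 4.4 | 5.3 |
| 90% v 65% | 71.7% to 76.6% | 5.0 | 2.3 | 3.2 | 4.9 |
| 85% v 60% | 64.1% to 70.0% | 5.8 | 3.3 | 3.9 | 6.6 |
| 80% v 55% | 58.6% to 65.8% | 7.2 | 3.9 | 5.2 | 8.4 |
| 70% v 40% | 72.5% to 76.4% | 3.9 | 0.3 | 0.4 | 1.4 |
| 60% v 30% | 72.5% to 76.4% | 3.9 | 0.2 | 0.2 | 0.4 |

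Over a wider grid at 40 v 40, where Fisher's power is 50 to 90%, the gain runs from 1.9 points (65% v 30%) to 8.0 points (75% v 50%), with a median of 4.5.

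**What changes in practice.** At 40 v 40, surgery in 35 v 27 patients (Fisher p = 0.059), 37 v 30 (0.066) or 39 v 33 (0.057) is not significant by Fisher. Each p-value lies below 0.0707, so Boschloo's test rejects. At 90% v 70%, Fisher needs 46 per arm (58.9% power) to come level with Boschloo at 40 (59.2%).

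**The case against.** The strongest reply is that Fisher's test is valid, pre-specified and customary for small arms, so replacing it is a matter of preference. That stands in one respect: the plan contains no error, bias or inflated error rate here. It does not remove the gain, because Boschloo's test gives the same guarantee and loses no Fisher rejection.

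The second reply is that Fisher's test is only half of the named primary analysis. The adjusted logistic regression does not share its conservatism. This also stands: a reader might infer that a borderline 52-week result would be declared negative because of Fisher's test alone, but the protocol does not make that test the sole decision rule. The unadjusted primary comparison still carries the loss.

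The third reply is that the size of the gain is unstable. Taking one patient from one arm raises Fisher's maximum size from 3.30% to 4.22% and, at 90% v 70%, cuts the gain from 5.8 to 2.3 points. That is correct, and it is why only a range is claimed.

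**Conclusion.** The point holds as an efficiency gain that costs next to nothing. Fisher's test is conservative at these arm sizes, and Boschloo's test typically recovers a few points of power: about 2 to 8 at 40 v 40, and near 0 to about 8 with slightly unequal arms. This rests on equal or nearly equal allocation, a two-sided 5% level for each comparison, and surgery rates that are assumed.

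Three stronger readings are not supported:
- **A ceiling of 3.3% on the error rate for about 40 per arm.** That figure belongs to exact 40 v 40 balance, which the plan does not guarantee.
- **A fixed loss of 5 to 7 points, or a size under 2% in this trial.** Both need surgery rates that the protocol does not state. Being listed for surgery does not settle the rate, because the Follow-up and Blinding sections let each patient decide at 10 weeks.
- **Power loss greatest when nearly all controls are operated on.** Size is lowest there, but the gain is 8.0 points at 75% v 50% against 5.8 at 90% v 70%.

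**What to change.** In the Statistical Analysis section, replace Fisher's exact test with Boschloo's two-sided exact test for each unadjusted surgery-rate comparison, in the ranking already given. Present each rate difference with an unconditional exact 95% confidence interval. Keep the adjusted logistic regression as planned.

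Name the version of the test: tables ordered by the two-sided Fisher p-value. Another version combines two one-sided 2.5% tests. It gave the same power at 40 v 40 in every scenario run, but differs with unequal arms: at 41 v 39 and 95% v 75% its gain is 0.0 points, against 4.9 for the two-sided ordering. The guarantee of keeping every Fisher rejection belongs to the two-sided ordering.

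The cost is a line or two of analysis text and a check that the software uses the named version. It needs no extra patients or data and gives up no control of type I error. The change should be made before unblinding.

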### Primary endpoint

1. The CTS symptom severity score change at 10 weeks after treatment:

1) 80 mg Methylprednisolone vs. placebo

2) 40 mg Methylprednisolone vs. placebo

3) 80 mg Methylprednisolone vs. 40 mg Methylprednisolone

2. The rate of surgery at (in rank order) 52 weeks, 24 weeks, and 12 weeks after treatment:

1) 80 mg Methylprednisolone vs. placebo

2) 40 mg Methylprednisolone vs. placebo

3) 80 mg Methylprednisolone vs. 40 mg Methylprednisolone

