## Discussion

In this double-blind placebo-controlled randomized trial of patients with moderately severe idiopathic CTS we intend to investigate the medium-term efficacy of steroid injection into the carpal tunnel and the possible presence of a dose-response relationship first at 10 weeks but also at 24 weeks and 52 weeks. The strength of this trial is that it will be performed at one orthopedic department to which the vast majority of patients with CTS from the study region are referred. In addition, steroid injection is rarely used as a treatment for primary idiopathic CTS by primary care physicians who usually treat patients with CTS in the study region before referring them to the orthopedic department.

A potential factor that may influence the results is that all patients are given the choice to have surgery at 12 weeks if their symptoms have not improved adequately. Before inclusion in the trial all the patients have unsuccessfully undergone treatment with wrist splinting and have symptoms of such severity that warranted referral to the orthopedic department. Because surgery is the only remaining treatment option with a strong evidence of efficacy there is no ethically acceptable alternative to offering surgery after 12 weeks. This trial will not answer the question of whether steroid injection is effective in patients with CTS that failed wrist splinting but the severity of which is judged by the patient as mild and not warranting surgery or in patients declining surgery for other reasons. The use of the standardized CTS symptom severity scale in the trial will show the severity spectrum of CTS in the study population. Another factor is the potential multiplicity of the analyses but this is addressed by providing a rank order with which the analyses will be carried out.

Our goal is to determine the efficacy of two different doses of local steroid injection in the treatment of moderately severe CTS, taking into account the natural course of CTS and the placebo effect of injection. During the first 24 weeks the safety of steroid injection in the carpal tunnel will also be evaluated in comparison with placebo. The results will also be useful to predict the effect of treatment with steroid injection related to severity of CTS. Information on possible relationship between dosage and duration of effect also will be provided by this study.

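### The rank order said to address multiplicity has no stop rule and does not link the two primary endpoints, so it does not hold the error rate at 5%

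*Protocol article*

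**What the plan says.** The Abstract names two primary outcomes: the 10-week change in symptom score and the surgery rate at 52 weeks. The Primary endpoint section numbers them 1 and 2. Under the first, "The CTS symptom severity score change at 10 weeks after treatment", it lists 80 mg vs placebo, 40 mg vs placebo and 80 mg vs 40 mg, in that order. Under the second it ranks three time points for surgery (52, 24, then 12 weeks) and lists the same three pairs.

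Two sentences deal with multiplicity. In Statistical Analysis, within the paragraph on surgery: "The issue of multiplicity is addressed by performing the analysis in the following priority; 52 weeks, 24 weeks, and 12 weeks". In the Discussion, of the analyses in general: "this is addressed by providing a rank order with which the analyses will be carried out".

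Statistical Analysis also says that "The primary analysis of rate of surgery will be done using Fisher's exact test (univariate) and logistic regression (multivariate"), the latter adjusted for baseline variables, and that results are to be given at every time point. It presents dose-response as something to be explored by giving priority to certain group comparisons. The only significance level in the article is in Sample Size: "With 90% statistical power, 5% significance level, and two-sided statistical tests".

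**The concern.** A fixed-sequence procedure protects the error rate because each test is allowed only when all tests before it were significant. Without that condition the order is merely the order of computation. The article names the order as its remedy and omits the condition.

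Two further gaps would remain even if a stop were understood. First, the two primary endpoints could each be tested at the full 5%. Second, the surgery comparisons are ordered on two separate axes: the text does not say whether 40 mg vs placebo at 52 weeks comes before or after 80 mg vs placebo at 24 weeks, so there is no defined point at which to stop. Each surgery comparison also has two tests under the label of primary analysis, with neither named as decisive.

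At stake is the meaning of a positive result. Efficacy could be claimed from one of several nominal 5% tests while the report says that multiplicity was handled.

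**Working it through.** **1. The plan's own figure.** The Sample Size inputs are "With 90% statistical power, 5% significance level, and two-sided statistical tests", "assuming a standard deviation of 1.0 for the CTS symptom severity score" and "the study can detect a true difference of at least 0.8 point on the CTS symptom severity score".

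- Normal approximation: n per arm = 2(1.960 + 1.282)² × 1.0² / 0.8² = 32.8, so 33.
- Exact noncentral t: 33 per arm gives 89.3% power and 34 gives 90.2%, so 34 per arm.
- Three equal arms: 3 × 34 = 102, which agrees with "when 102 patients have been randomized". Equal allocation is an assumption, as the article gives no ratio.

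The figure is right. It uses 5% for one steroid arm against placebo on the score.

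**2. Number of comparisons.** Score: 3 pairs. Surgery: 3 pairs × 3 time points = 9. Total 12. Limited to the Abstract's time points (10-week score, 52-week surgery): 6, of which 4 are against placebo.

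**3. Each endpoint gated separately at 5%.** With no true effects, a false positive occurs only if the first test on one endpoint or the other is significant.

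- Upper bound: 5% + 5% = 10%.
- Independent tests of exact size: 1 − 0.95² = 9.75%.
- Fisher's test is conservative. At 40 per arm and an assumed 65% surgery rate its actual size is 2.8%, giving 1 − 0.95 × 0.972 = 7.7% under independence.

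**4. Simulation with no true effects.** There were 40,000 trials per scenario with 40 per arm (120 / 3), t-tests on the score in place of the mixed model, and Fisher's test on surgery. The document gives neither surgery rates nor a score-surgery correlation, so both are assumed and varied: rates at 12/24/52 weeks of 40/55/65%, 50/55/65%, 60/65/80% and 60/75/85%, and correlations of 0, 0.3, 0.6 and 0.9.

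| Tests that can support a claim | Chance of at least one false positive |
|---|---|
| One sequence over both endpoints, with a stop | 5% |
| Each endpoint gated separately at 5% | about 6-8% (simulated 6.6-7.8%) |
| Four placebo comparisons, no gating | about 12-14% |
| All 12 listed comparisons, no stop | about 21-26% |

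With an uncorrected test of near-nominal size on surgery, the second row becomes about 8-10% and the last about 29-35%. That test is not the planned adjusted logistic model, so these figures are only indicative. Treating all 12 tests as independent gives 1 − 0.95¹² = 46%, which overstates the error because the comparisons share arms and patients.

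**5. Splitting alpha instead.** At 2.5% per endpoint, power for 0.8 is 84.0% with 34 per arm and 89.9% with 40. Reaching 90% takes 41 per arm, or 123 evaluable patients.

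**The case against.** The strongest reply is that offering a rank order as the answer to multiplicity is ordinary shorthand for hierarchical testing, and that the stop condition is operational detail for a full protocol or analysis plan, which is not shown. The endpoints are numbered 1 and 2, only the score is powered, and the Discussion's sentence is not limited to the surgery time points. Read as one gated sequence over both endpoints, the plan would have a 5% error rate.

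That reading is possible, and silence on the detail would be no finding. But the article is not silent: it says the problem is addressed and names a device that does not do so by itself. The ranking words in Primary endpoint are attached only to the surgery time points, and no sentence makes surgery conditional on the score. The two surgery orders also stay unmerged on any reading.

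Other parts of the reply stand. A reader might infer that the trial runs at a 21-26% error rate. The documents do not support that as the expected figure: the Abstract names only 52-week surgery as the surgery primary, dose-response is described as explored, and 80 mg vs 40 mg cannot by itself show efficacy against placebo. A reader might also infer that the sample size is wrong because it uses the full 5% on one comparison. It is not, since the first test of any fixed sequence does the same. Nor does presenting odds ratios at every time point show that each is confirmatory; that is reporting, which a hierarchy allows. Finally, the article does not expressly promise a family-wise 5%. The point rests on its statement that multiplicity is addressed. Pairing an unadjusted with an adjusted test is common practice; what is missing is which one decides.

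**Conclusion.** The concern holds. The stated device does not control the error rate, because no later test depends on an earlier one and the two primary endpoints are not joined. The realistic size runs from about 6-8%, if each endpoint is gated separately, to about 12-14%, if the four placebo comparisons are all open. The 21-26% for 12 comparisons is a worst case. All these figures assume 40 per arm, Fisher's test, and surgery rates and correlations that the document does not give. The direction does not depend on those choices: error exceeded 5% in every scenario in which the endpoints were left unlinked. One gated sequence over both endpoints would remove the inflation, as would a rule that both must succeed combined with a stop rule within each endpoint. Neither is written.

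**What to change.** State one fixed sequence at two-sided 5%, stopping at the first non-significant test, in the order that Primary endpoint already uses:

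1. 10-week score: 80 mg vs placebo, 40 mg vs placebo, 80 mg vs 40 mg.
2. 52-week surgery, in the same dose order.
3. 24-week and then 12-week surgery, in the same dose order.

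The 80 mg vs 40 mg comparisons may be moved to the end or labelled exploratory, so that they do not block the surgery tests. Name either Fisher's test or the adjusted logistic model as decisive for surgery and the other as sensitivity. Everything after the stop is descriptive and can still be reported with estimates and intervals.

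The sample size stays as it is and the first test keeps its 90% power. The price is that later comparisons, surgery included, cannot be claimed once an earlier one fails. Moving surgery ahead of the 40 mg score test is not advised on power grounds. The article gives no power calculation for surgery, and for an assumed 80% vs 60% at 40 per arm Fisher's test has about 41% power, so it would often block a comparison to which the stated 90% applies.

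If the sponsor does not want a stop rule, the article should withdraw the statement that multiplicity is addressed and name one confirmatory comparison. Either change is one of wording and should be made before unblinding.

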### Inclusion Criteria

The inclusion criteria (Table 1) are primary, idiopathic CTS, age 18 to 70 years, either gender, symptoms of classic or probable CTS according to the diagnostic criteria in the Katz hand diagram [16], symptom duration of at least 3 months, inadequate response to wrist splint, nerve conduction tests showing median neuropathy at the wrist and no other abnormalities or, in the presence of normal nerve conduction test results, two orthopedic surgeons independently diagnose the patient with CTS, and symptom severity of such magnitude that the patient is willing to undergo surgery.

**Table 1 T1:** Eligibility criteria

Inclusion criteria	Exclusion criteria
Primary, idiopathic CTS	Previous steroid injection in same wrist
Age 18-70 years	Inflammatory joint disease
Either gender	Diabetes mellitus
Classic or probable CTS according to the diagnostic criteria in the Katz hand diagram	Polyneuropathy
Symptom duration of at least 3 months	Vibration induced neuropathy
Inadequate response to wrist splint	Pregnancy
Abnormal nerve conduction tests or, if normal, CTS diagnosed independently by 2 surgeons	Trauma to affected hand in preceding year
Patient willing to undergo surgery	Previous surgery for CTS on affected hand
	Surgery for CTS on contralateral hand in preceding 2 months
	Inability to respond to questionnaires
	Severe sensory loss (two-point discrimination >8 mm)
	Thenar atrophy
	Severe medical illness
	Drug or alcohol abuse

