### Outcome Measures

The CTS symptoms severity scale is a validated 11-item questionnaire that mainly inquires about severity, frequency and duration of night and daytime pain and numbness or tingling [14,15]. The CTS score ranges from 1 (no symptoms) to 5 (most severe symptoms). The *Quick*DASH is a validated 11-item questionnaire that mainly inquires about difficulties in performing daily activities, yielding a score from 0 (no disability) to 100 (worst possible disability) [18]. The SF-6D is a validated health utility measure that is used to compare cost-effectiveness of different treatments and the value ranges from -0.11 (worst health) to 1.0 (perfect health) [19]. All AEs are recorded during 24 weeks. Duration of sick leave for employed patients is recorded.

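### The severity and duration subgroup analyses are fixed only as two-class splits, an inefficient basis for predicting the treatment effect by severity; continuous interaction terms should be added.

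*Protocol article*

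**What the plan says.** The Statistical Analysis section announces three subgroup analyses with the words "We will conduct the following predefined subgroup analyses". The one for severity is given as "symptom severity (baseline symptom severity score below 3.0 versus 3.0 or higher"). The one for duration cuts at 12 months, and the third sets the two higher grades of nerve conduction abnormality against the two lower ones. Each has two classes. No reason is given for the cut-offs, and no analysis with score or duration as a continuous modifier is described. The outcome to which the subgroup analyses apply is not named.

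The score is an 11-item scale, described under Outcome Measures: "The CTS score ranges from 1 (no symptoms) to 5 (most severe symptoms"). The cut at 3.0 is therefore the midpoint of the scale. Duration is bounded below by the inclusion criterion "symptom duration of at least 3 months". The Discussion states: "The results will also be useful to predict the effect of treatment with steroid injection related to severity of CTS".

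**The concern.** Symptom score and duration are close to continuous. A cut at 3.0 treats scores of 2.9 and 3.0 as different and scores of 3.0 and 5.0 as alike. It gives two class averages, whereas a statement about prediction by severity calls for the effect across the range of severity.

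Two things are at stake. A real gradient may be missed because the split discards information. And if the class results are read side by side, chance may produce a significant result in one class only, which is easily taken for dependence on severity.

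**Working it through.** **Inputs.** From the Sample Size section: "With 90% statistical power, 5% significance level, and two-sided statistical tests", SD 1.0, detectable difference 0.8, 102 patients randomized, 120 to be enrolled. Assumptions, because the article does not give them: equal allocation (34 or 40 per arm), the 10-week symptom score as the outcome, SD 1.0 within each class, and the distributions of baseline score and duration.

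**The plan's own figure.** A two-sample t test with 34 per arm, difference 0.8 and SD 1.0 has 90.2% power, and 3 × 34 = 102. The stated sample size reproduces. At 40 per arm the power is 94.2%.

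**Information kept by a split.** For a linear effect, the share kept is the squared correlation between the marker and its class indicator. For a normal marker cut at c, with proportions p and 1 − p on either side, it is φ(c)² / [p(1 − p)].
- At the median: 0.3989² / 0.25 = 0.637, so 36% is lost.
- Lost at other splits: 38% at 60/40, 42% at 70/30, 46% at 75/25, 51% at 80/20.
- Score as a normal truncated to 1–5, cut at 3.0, assumed mean 2.6 to 3.4 and SD 0.6 to 1.0: 32% to 45% lost.
- Score uniform on 1–5: 25% lost.
- Log duration, lognormal from 3 months, assumed median 12 to 24 months and log-SD 0.6 to 1.0, cut at 12: 35% to 61% lost.
- A true threshold exactly at the cut: nothing lost.

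**Detectable difference in effect between two classes.** SE = SD × √[(1/n₁ + 1/n₂) / (p(1 − p))]; for 80% power multiply by 1.96 + 0.84 = 2.80.
- 40 v 40, even split: √(0.05 / 0.25) = 0.447, giving 1.25 points.
- 40 v 40, 25/75 split: √(0.05 / 0.1875) = 0.516, giving 1.45 points.
- 34 v 34, even split: 0.485, giving 1.36 points.
- Pooled steroid 80 v placebo 40, even split: 0.387, giving 1.09 points (from the unrounded SE).

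All exceed the 0.8-point target for the main effect.

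**Separate class tests when the true effect is 0.8 in everyone.** At 20 v 20 per class the power is 69.3%, against 94.2% for 40 v 40 without the split.
- Both classes significant: 0.693² = 48%.
- Exactly one significant: 2 × 0.693 × 0.307 = 43%.
- Neither: 0.307² = 9%.

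With pooled steroid, 40 v 20 per class has 82% power, and exactly one class is significant about 30% of the time.

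**What a continuous term gains.** Take a normal marker and a linear gradient whose mean effect differs by 0.8 point between the two classes. At an even split the class means lie 0.3989 / 0.25 = 1.596 SD apart, so the slope is 0.8 / 1.596 = 0.501 per SD of the marker. Its SE is SD × √(1/n₁ + 1/n₂), which is 0.224 at 40 v 40.

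| Comparison | Split | Two classes | Continuous |
|---|---|---|---|
| 34 v 34 | 50/50 | 38% | 54% |
| 34 v 34 | 70/30 | 33% | 51% |
| 40 v 40 | 50/50 | 43% | 61% |
| 40 v 40 | 70/30 | 37% | 58% |
| 80 v 40 pooled | 50/50 | 54% | 74% |
| 80 v 40 pooled | 70/30 | 47% | 70% |

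The continuous term has more power in every row, and none reaches 90%.

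**The case against.** The case for leaving the plan alone has several sound parts. The cut-offs are fixed in advance, which prevents a choice driven by the data. The subgroup analyses are neither primary nor secondary endpoints. The sentence on severity is a single remark in the Discussion. A condensed article may leave the test details and the reasons for the cuts to a fuller document, so their absence is no fault. Sample size limits the question under either method. All of this stands, and it keeps the point small.

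It also rules out four stronger readings that a reader might infer.
- That prediction by severity cannot be delivered. The Discussion promises only results useful for prediction. Three subgroup analyses, one of them on nerve conduction grade as a second measure of severity, give a coarse answer, and a continuous analysis is not excluded.
- That a third or more of the information is always lost. This depends on the distribution and on the shape of the effect, neither of which is given.
- That disagreement between the classes is the expected result. At 20 v 20 per class it occurs 43% of the time, but both classes are significant 48% of the time.
- That the authors will rest claims on significance within a class, or that 3.0 splits the sample badly. The article says neither, and gives no baseline distribution.

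The objection does not remove the point that the two-class form is the one the article fixes, and that a more efficient form is available from the same data.

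**Conclusion.** The point holds as a low-cost improvement to exploratory analyses. The loss is about 36% of the interaction information at a median split for a roughly normal marker with a linear gradient, and more at uneven splits. It falls to 25% for a uniform score and to zero for a threshold at the cut. The 1.25-point detectable difference and the 43% disagreement rate rest on equal arms of 40, SD 1.0 and an even split; the 43% also supposes a pairwise comparison and separate tests in each class, which the article does not specify. The primary and secondary endpoints and the sample size calculation are unaffected.

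**What to change.** Make the predefined effect-modification analysis a treatment-by-baseline interaction, with symptom score and log symptom duration as continuous variables and their main effects in the model. The primary mixed model uses the baseline score as one of its repeated outcomes. The severity model should instead use it as a covariate, with the post-injection scores as outcome.

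Report the estimated effect with its 95% confidence interval across the observed range. Keep the 3.0 and 12-month classes for display. Base any statement on prediction by severity on the interaction estimate, and label it exploratory because of the limited power shown above.

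The cost is a change of wording and a little analysis; the data are already to be collected. The one downside is that the model assumes a smooth gradient, which can be checked against the displayed classes.
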